#### Sleep quality

Sleep quality is measured by the 19-item Pittsburgh Sleep Quality Index (Chinese version; CPSQI) [22]. Respondents rate their subjective sleep quality on a “0–3” Likert scale, with higher scores representing poorer sleep quality. The Cronbach’s alpha and test–retest reliability of the CPSQI are 0.82 and 0.77, respectively, with good discriminant validity when used in the Chinese population [25].

#### Physical fitness

Physical fitness is measured by Rockport Fitness Test [26]. This predictive submaximal test requires the participants to walk as fast as possible on a 200-m track for eight rounds during which the individuals can slow down or rest if needed, but instruction to encourage walking will be given. HR will be taken with a HR monitor at the end of every 400 m. A regression equation is used to compute the predicted maximal oxygen uptake (VO_2max_) using the track walk time, fourth quarter HR, body weight, age, and gender. The test–retest reliability is 0.97 and the predicted VO_2max_ demonstrated high correlation (r = 0.93) with the actual VO_2max_ in older adults [26]. Implementation of the test follows the guidelines of the ACSM and BP, HR, and contradictory symptoms will be assessed before the walking test.

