### Outcome variables

Sleep pattern and sleep quality are the primary outcomes whereas physical fitness and mood status are the secondary outcomes and mediating variables. The following methods will be used to measure these outcomes at baseline and upon the completion of training. Various potential confounders including demographic background, health profile, and expectation on treatment credibility will also be measured.

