#### Demographic and health profiles

Participants’ demographic and health profile including age, gender, education level, marital status, living conditions, lifestyle, and medical and drug history will be collated.

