### Data processing and analysis

Data will be double-entered for validation and analyzed on an intention-to-treat (ITT) basis. Skewed variables will be transformed before being subjected to analyses. Baseline characteristics between the two arms of participants will be compared using t test, chi-square test or Fisher’s exact test, as appropriate. Mixed effects models will be used to compare the differential changes on the primary (sleep pattern and quality) and secondary (physical fitness and mood status) outcomes across the baseline and post-test (T2) between the two study arms, with adjustment for the potential control variables (i.e. expected treatment credibility, demographic and health profile) which are statistically non-equivalent at baseline (*p* < 0.25). In particular, a dummy variable (group) will be assigned to represent the exercise training group (i.e. treatment group) with the health education group (i.e. control group) as reference, and another dummy variable (time) will be set to indicate the time points (1 = post-test, 0 = pre-test) in the mixed effects model. To accurately identify the effects of the exercise training, an interaction term group × time will also be included in the model to assess the difference in the change of each outcome across the pre-test and post-test period (i.e. pre-post change) between the two study groups. The statistical significance of the model coefficients, including the interaction term, will be assessed by Wald test. The strengths of mixed effects model lie in accounting for intra-correlation between repeatedly measured data and accommodating missing data caused by dropout, provided the data are missing at random [26]. This method is most suitable for ITT analysis without the need for missing data imputation. All analysis will be conducted by using SAS release 9.3 (SAS Institute Inc, Cary, NC) at a 5% level of significance. Depending on the data distribution, the mixed effects modeling will be performed using the PROC MIXED or NLMIXED.

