Path analysis is used to examine the mediating roles of physical fitness and mood status on the effect of exercise training on sleep pattern and quality with adjustment for the above control variables. Based on our hypothesized mediation model (Fig. 1), a baseline path model using the baseline data will be built first. To which path model with the same structure for T2 is added and linked by intra-correlations among the same variables. The final mediation model will then consist of two clusters (corresponding to the two time points) and are linked by the intra-correlations. The equality of a specific path coefficient in the two clusters can be assessed by imposing equality constraint on the coefficient and tested using a nested goodness-of-fit test [27]. The mediation effects of physical fitness and mood status on the effect of exercise training on sleep pattern and quality will be assessed through the significance of the corresponding products of indirect path coefficients from exercise training to sleep pattern and quality, respectively [28]. In view of the possibility of violation of normality assumption, a bootstrapping approach [28], instead of the conventional multivariate delta method, will be used to estimate the standard errors and the confidence intervals of the product terms (mediation effects). Furthermore, the effect of exercise training (as compared to control) on the change of the path coefficients to the sleep pattern and quality outcomes directly or by way through the mediators (physical fitness and mood status) over time can be assessed using the three-way interactions approach [27]. The path analyses and the bootstrapping will be performed using Mplus Version 6 and the parameters will be estimated by mean and variance adjusted weighted least square method (WLSMV). The bootstrapping estimations of the standard errors and confidence intervals will be performed using bias-corrected bootstrapping method with 10,000 replications [28]. The overall fit of the path models is assessed using comparative fit index (CFI), root mean square error of approximation (RMSEA), and standardized root mean square residual (SRMR), with CFI > 0.95, RMSEA < 0.06, and SRMR < 0.08, indicating a good data-model fit [27].

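### The mediation path model picks its covariates by baseline imbalance between arms, so the fitness-to-sleep path can stay confounded by age, gender and body weight, all three of which are terms in the fitness score

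*Protocol article*

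**What the plan says.** Under Outcome variables, the protocol article states that "physical fitness and mood status are the secondary outcomes and mediating variables". Its Physical fitness section defines fitness as predicted VO2max from a walking test, obtained by a regression equation "using the track walk time, fourth quarter HR, body weight, age, and gender".

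Under Data processing and analysis, the mixed models adjust for potential control variables ("i.e. expected treatment credibility, demographic and health profile) which are statistically non-equivalent at baseline"), with p < 0.25 as the threshold. The path analysis takes over the same set: it is run "with adjustment for the above control variables". Mediation is judged by the "significance of the corresponding products of indirect path coefficients from exercise training to sleep pattern and quality", with bias-corrected bootstrap intervals. The model has a baseline cluster and a post-test cluster, "linked by intra-correlations among the same variables".

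The candidate variables are described under Demographic and health profiles as including "age, gender, education level, marital status, living conditions, lifestyle, and medical and drug history". Age and gender are there. Body weight is not named, although it is needed for the VO2max equation.

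**The concern.** A mediated effect is the product of two paths. Random allocation makes the first one, exercise to fitness, a fair comparison. The second, fitness to sleep, is an observational association among participants within arms. Anything that drives both fitness and sleep confounds it, and this is so however well the arms are balanced. Choosing covariates because they are "which are statistically non-equivalent at baseline" therefore answers the wrong question for this path: a variable can be perfectly balanced between arms and still confound it.

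The fitness mediator makes the problem plain, because three obvious candidate confounders are inputs to its formula. If age, gender or weight is also related to sleep, part of that relation is carried by the fitness-to-sleep coefficient. When exercise raises the score, the product can then reach significance although fitness itself does nothing for sleep.

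What is at stake is Hypothesis 2, the first of the secondary aims, and the reason why the sample size was raised from 104 to 112 per arm.

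**Working it through.** **Inputs from the protocol.** 112 per arm with 10% attrition: 112 × 0.9 = 100.8, which agrees with the stated 100 per arm. Covariate gate p < 0.25. Test level 5%.

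**Inputs assumed, because the protocol gives no values.** R² is the share of predicted VO2max variance explained by age, gender and weight together: 30-50%. r is their joint correlation with sleep: 0.1-0.3, with all three acting in aligned directions. a is the exercise effect on the score: 0.4 SD (the protocol's own 0.4 refers to the sleep outcomes). The true fitness-to-sleep effect is zero.

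**Step 1: how often the gate admits the variables.** Under randomisation a baseline p-value is uniform, so each variable passes with probability 0.25. Treating age and gender as independent:
- both enter: 0.25² = 0.0625, about 6%;
- neither enters: 0.75² = 0.5625, about 56%;
- at least one is left out: 1 − 0.0625 = 0.9375, about 94%.

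**Step 2: size of the bias with no adjustment.** In within-arm SD units, the fitness-to-sleep slope produced by the omitted variables is b = √R² × r, and the spurious mediated effect is a × b.
- R² = 0.3, r = 0.1: b = 0.548 × 0.1 = 0.055; a × b = 0.022 SD.
- R² = 0.4, r = 0.2: b = 0.632 × 0.2 = 0.126; a × b = 0.051 SD.
- R² = 0.5, r = 0.3: b = 0.707 × 0.3 = 0.212; a × b = 0.085 SD.

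**Step 3: how often that is declared significant (middle case, no covariates).** Exercise-to-fitness path: z = 0.4 / √(2/100) = 2.83, power Φ(2.83 − 1.96) ≈ 0.81. Fitness-to-sleep path: SE ≈ √((1 − 0.126²)/200) = 0.070, z = 1.80, rejection probability Φ(1.80 − 1.96) ≈ 0.44. Both: 0.81 × 0.44 ≈ 0.36, in line with 35% by simulation.

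**Step 4: simulation of the gated rule.** 100 per arm, joint test of both paths at 5% as a stand-in for the bootstrap, weight not eligible for entry. Range over r = 0.1 to 0.3:

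| Covariates in both equations | R² = 30% | R² = 50% |
|---|---|---|
| None | 10-50% | 13-69% |
| Gate p < 0.25 on age and gender (the plan) | 9-42% | 12-63% |
| Age, gender, weight always | 4-5% | 4-5% |

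At the mid-range (R² = 40%, r = 0.2), with all three variables eligible for the gate, the rates were 35% with no covariates, 26% gated and 5% with all three forced in.

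**Step 5: sensitivity.**
- *Smaller share.* At R² = 20% the gated rate is 7-29%; at 10% it is 5-18%.
- *Opposite direction.* If one of the three variables relates to sleep in the opposite direction, the gated rate falls to about 5-11%. The fall is smaller if that variable is age or gender, since the gate can then admit it and remove the offset.
- *Two-cluster model.* Fitting the baseline and post-test clusters, linked only by correlations, to population covariances without covariates leaves 49-98% of the bias in the slope (0.066/0.134 = 0.49 to 0.228/0.232 = 0.98), over assumed between-time correlations.

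**The case against.** The strongest reply concerns where the fault lies. True VO2max also varies with age, sex and weight, and the protocol cites a correlation of 0.93 between predicted and actual VO2max in older adults. A reader might infer that the formula makes part of the score something other than fitness. The documents do not support that. A directly measured VO2max would be confounded in the same way, and so would walk time and heart rate. The fault is the covariate rule; the formula only makes it easy to see.

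A reader might also infer that leaving out age and gender wastes power for fitness as a secondary outcome. It does not: that analysis tests group × time in a pre-post mixed model, where fixed characteristics largely cancel.

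The size is open to challenge too. It rests on inputs that the protocol does not give. The sample is restricted (aged 60 or over, little exercise, moderate complaints only), and aligned directions are an assumption. The higher no-covariate rates are not the plan's rates, because at least one of age and gender enters in about 44% of trials (1 − 0.5625). The two-cluster structure takes away some of the bias. All of this limits the magnitude.

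The absence of body weight from the profile is weak evidence, since the list is introduced as non-exhaustive in a condensed article. None of these points makes a between-arm p-value a sound way to choose confounders of a non-randomised path.

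**Conclusion.** The concern holds as a fault in the covariate rule for the mediation model. Following the plan as written, false mediation by fitness would be declared in about 9-63% of trials under the assumed inputs, against 4-5% with age, gender and weight always included. With one variable acting in the opposite direction the rate is about 5-11%, close to nominal, so a false claim is possible but not inevitable. The bias appears only if exercise changes the score and if these variables relate to sleep. It inflates the claim when the directions align and could mask mediation when they oppose. The simulated rates come from a post-test regression, so the planned two-cluster model would give somewhat less bias, but not none.

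A reader might go further and doubt the trial's main result. The documents give no ground for that: the exercise-versus-control comparison of sleep does not use the fitness-to-sleep path. The point is worth correcting because mediation is a stated hypothesis and the correction is nearly free.

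**What to change.** State in the analysis plan that every path model using predicted VO2max includes age, gender and body weight, all as measured at baseline, as covariates in both the fitness and the sleep equations, whatever the arm comparison shows. Post-test weight should not be used, because it may respond to exercise. As a supportive run, replace the score by walk time and fourth-quarter heart rate as the mediator, with the same three covariates. No change is needed on this account to the mixed model for fitness as a secondary outcome.

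The cost is a sentence or two in the plan and a few degrees of freedom in about 200 participants. All three variables are already recorded for the VO2max equation.

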#### Mood status

Mood status will be measured by the 30-item Profile of Mood States Short Form (POMS-SF, Chinese version) [27], which covers tension-anxiety, depression-dejection, anger-hostility, vigor-activity, fatigue-inertia, and confusion-bewilderment. A 5-point response scale is used with higher score representing higher mood disturbance. The Cronbach’s alphas were in the range of 0.67–0.90 and the PSOM-SF has been widely used to measure mood disturbance associated with poor sleep.

#### Expectation on treatment credibility

Expectation on treatment credibility refers to the respondent’s expectation of the sleep-promoting effect of the received intervention. A four-item questionnaire is used, which rates the (1) reasonableness of treatment, (2) opinion of the therapist, (3) expectation for improvement, and (4) likelihood to recommend the treatment to others, on a 10-point scale, with a higher score indicating a better expectation [28].

#### Demographic and health profiles

Participants’ demographic and health profile including age, gender, education level, marital status, living conditions, lifestyle, and medical and drug history will be collated.

### Method of randomization and data collection procedure

The social workers in the study settings will help to identify potential individuals for screening. Figure 3 outlines the data collection procedure (SPIRIT figure; SPIRIT 2013 Checklist is appended in the Additional file 1). The RA1 will screen the participants’ eligibility in the community center and obtain their informed consents for participation. Whenever there are about 20 individuals being recruited, s/he will conduct the Rockport Fitness Test to the participants inside the community center and collect data on their demographic and health profile, sleep quality (PSQI), and mood status (POMS-SF). Then, the RA1 will distribute an actiwatch to each individual. S/he will teach them how to: (1) wear and remove the watch for the ten-day recording on sleep pattern (the first three days are for desensitization and data will not be used); and (2) record the in-bed and out-bed time on a simple log book. The part-time research nurse (RA2) will then collect the returned actiwatches after one week in the community center and randomly assign the participants to the study arms.

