Power analysis is used to estimate the sample size estimation for pre-test–post-test study with attrition [15]. According to two pilot-scale studies which examined the effects of moderate-intensity endurance exercise on sleep among older adults [11, 13], the effect sizes of exercise interventions on sleep quality and pattern were in the range of 0.21–1.55 (Cohen’s d). Hence, this study aims to detect a small to medium effect size of 0.4 on the primary sleep pattern and quality outcomes. Using the program RMASS2, it is estimated that a sample size of n = 104 participants per study arm would give the study 80% power at a 5% level of significance to detect the targeted effect size of exercise, assuming randomization will render the two arms equal at baseline and allowing for a 10% attrition. As this study also aims at examining the mediating process between exercise and sleep, consideration is also given to the sample size requirement for path analysis using structural equation modeling approach. According to Loehlin, a sample size of at least 100 and preferable ≥ 200 is required to ensure the statistical power for conducting structural equation modeling [16] and thereby increasing the sample size to 112 individuals per study arm, in allowing for a 10% attrition, to attain the recommended total sample size of 200 participants (i.e. 112 × 0.9 = 100 per arm).

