#### Sleep pattern

Sleep pattern refers to total sleep time (TST), time to initiate sleep (sleep latency [SL]), number and duration of wakening after sleep onset (WASO), and ratio of TST and the time spent in bed (sleep efficiency [SE]). These parameters will be measured by an actiwatch from the company called ActiGraph, which is a 3.5 × 3.5 × 1 cm watch. It contains an accelerometer to record the intensity and frequency of body movement during sleep. Individuals will wear the actiwatch on the non-dominant wrist during sleep for one-week’s continuous night monitoring. They are required to record the daily in-bed and out-bed time on a simple log book. To retrieve the parameters of sleep pattern, the actiwatch will be connected via a USB port to the ActiTrainer Online Management Platform. With the input of in-bed and out-bed time, an algorithm will translate the raw acceleration data to the sleep parameters. The actiwatch has extensive use in research and is well correlated with the findings on polysomnography [24].

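### The baseline actigraphy procedure contradicts itself: a ten-day recording with three days discarded, but watches collected and participants randomised after one week, which would leave four usable nights instead of seven

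*Protocol article*

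**What the plan says.** All places are in the protocol article.

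- **Outcome variables** gives actigraphy primary status: "Sleep pattern and sleep quality are the primary outcomes whereas physical fitness and mood status are the secondary outcomes and mediating variables". Under **Sleep pattern**, total sleep time, sleep latency, wakening after sleep onset and sleep efficiency are all derived from the actiwatch.
- **Sleep pattern** sets the monitoring period: "Individuals will wear the actiwatch on the non-dominant wrist during sleep for one-week’s continuous night monitoring". It mentions no run-in.
- **Method of randomization and data collection procedure** says that the first research assistant teaches participants to "wear and remove the watch for the ten-day recording on sleep pattern", and adds that "the first three days are for desensitization and data will not be used".
- The same paragraph then says that the research nurse "will then collect the returned actiwatches after one week in the community center and randomly assign the participants to the study arms".
- Later in that section, the assigned intervention is to start within two weeks of the baseline measure.

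**The concern.** The ten-day recording and the collection after one week stand in adjacent steps of one operating procedure. If both are counted from the day the watch is distributed, the recording is unfinished when the watch is taken back. The collection step is also the point at which participants are randomised, in blocks of about 20, so staff who follow it would cut the recording short for a whole block at once. Baseline nights lost this way cannot be recovered once the intervention has begun.

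At stake is the precision of the baseline value of every sleep-pattern parameter. A person's mean over fewer nights carries more night-to-night variation, and this passes into the pre-post change that the group-by-time term compares between arms.

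**Working it through.** **1. Night count (figures from the article).** Usable nights = recorded nights - discarded nights.

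| Instruction followed | Recorded | Discarded | Usable |
|---|---|---|---|
| Ten-day recording | 10 | 3 | 7 |
| Collection after one week | 7 | 3 | 4 |

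The first row reproduces the one week given under Sleep pattern. The second loses 3 of 7 nights (43%).

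**2. Noise in a person's mean (illustration).** The article gives no night-to-night reliability, so I assume a single-night intraclass correlation (ICC) of 0.3 to 0.5. With single-night variance set to 1, the variance of a k-night mean is v(k) = ICC + (1 - ICC)/k, and its reliability is ICC/v(k).

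| ICC | v(7) | v(4) | v(4)/v(7) | Reliability, 7 nights | Reliability, 4 nights |
|---|---|---|---|---|---|
| 0.3 | 0.400 | 0.475 | 1.19 | 0.75 | 0.63 |
| 0.4 | 0.486 | 0.550 | 1.13 | 0.82 | 0.73 |
| 0.5 | 0.571 | 0.625 | 1.09 | 0.88 | 0.80 |

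**3. Power for the pre-post change (illustration).** Further inputs:

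- a true-level pre-post correlation of 0.7 (assumed);
- the article's effect size of 0.4, taken to be in units of the SD of a seven-night mean (assumed);
- 112 × 0.9 = 100.8 analysed per arm (from the sample-size paragraph);
- two-sided 5% (two-sided assumed), noncentral t.

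With a baseline nights and b post-test nights, the change variance is v(a) + v(b) - 2 × 0.7 × ICC. The standardised effect is 0.4 × √v(7) divided by the square root of that variance.

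For ICC 0.4, where 2 × 0.7 × 0.4 = 0.56 and 0.4 × √0.4857 = 0.2788:

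- 7 and 7 nights: 0.4857 + 0.4857 - 0.56 = 0.4114; effect 0.435; power 87%.
- 4 and 7 nights: 0.5500 + 0.4857 - 0.56 = 0.4757 (up 16%); effect 0.404; power 81.5%.
- 4 and 4 nights: 0.5500 + 0.5500 - 0.56 = 0.5400 (up 31%); effect 0.379; power 76%.

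Over the assumed ICC range:

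| ICC | 7 and 7 | 4 and 7 | 4 and 4 |
|---|---|---|---|
| 0.3 | 83% | 75% | 69% |
| 0.4 | 87% | 81.5% | 76% |
| 0.5 | 89% | 86% | 82% |

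**4. The stated sample size.** The sample-size paragraph, under Study settings and participants, says that "this study aims to detect a small to medium effect size of 0.4 on the primary sleep pattern and quality outcomes". No number of nights is shown among its inputs, so these figures illustrate sensitivity and do not correct the stated 80%.

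**The case against.** The strongest reply is that this is a slip in one phrase. Ten less three is seven, so the ten-day rule and the one week under Sleep pattern agree, and participants are taught the ten-day rule. Two statements point to seven nights and one to four. The collection week might even be counted from the end of the three run-in days.

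Much of this stands. A reader might infer a three-way conflict, but the one week under Sleep pattern fits as the number of analysed nights. A reader might also infer that the trial plans to analyse four nights. The article does not say so, and seven is the likelier intent. What remains is that the text does not count the collection week from the end of the run-in, and the collection sentence is an instruction to staff that triggers randomisation.

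Two further inferences are tempting and unsupported. One is that baseline and post-test follow different run-in rules, so that the pre-post change carries a first-nights artefact. Outcome variables applies the same methods at both time points, and nothing states a different post-test rule. The other is that power falls from 87% to 76% as a matter of fact. That needs four nights at both time points, whereas the collection sentence describes baseline only, and it rests on an ICC and a correlation that are not in the article.

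**Conclusion.** The contradiction is real but narrow. It lies within the section on randomization and data collection, between the length of the recording and the time of collection. Followed as written, the collection sentence leaves four baseline nights instead of seven for a primary outcome. That conclusion needs only the article's own figures.

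The direction of the effect, a noisier baseline, is firm, but its size is not. If only baseline is cut, the loss is about 5 percentage points of power at the assumed ICC of 0.4, and about 4 to 7 points over ICC 0.3 to 0.5. The larger loss, about 10 points at ICC 0.4, applies only if post-test recording is cut in the same way. The point deserves correction because the error would act on whole blocks, cannot be undone after the intervention starts, and is cheap to prevent.

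**What to change.** - In Method of randomization and data collection procedure, change the collection sentence so that watches are returned after the tenth night and randomisation follows.
- Under Sleep pattern, define each parameter as the mean of nights 4 to 10, and state that the same rule applies at baseline and post-test.
- Recruitment was ongoing when the article was written, so check how many nights the blocks already randomised actually recorded, and report it.

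The cost is about three more days before each watch comes back and slightly slower turnover of watches. If the two-week limit for starting the intervention is counted from watch distribution, 14 - 10 = 4 days remain for randomisation and the start of the programme. That is tighter, but it fits.
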